### Power Calculation

A sample size of 150 participants per group has been estimated based on detecting a difference in help-seeking behavior (25% vs 10%) with 80% power at a 5% significance level using G*Power 3.1, allowing for up to 33% attrition commonly observed in minimally guided digital interventions [26]. These include interventions delivered through digital platforms, which often vary widely in design and outcomes. Consequently, closely comparable studies for precise sample size estimation were difficult to identify, and the current estimate is informed by findings from studies with broadly similar characteristics [14,27].

### Procedure

Participants will be randomized into either the intervention or control group in a 1:1 ratio, using a computer-generated randomization sequence. The randomization list will be generated by the study supervisor. Stratified randomization will be used based on age group (18-35 years and 36 years and above) and gender to ensure balance across key demographic variables.

A brief telephonic interview for eligibility screening will be conducted after all other questionnaires are completed. This call allows the researchers to clinically assess the current mental state and amenability to take part in the study process, inquire whether participants have sought consultation for any psychiatric problem in the past or recent times, and confirm willingness to participate.

Eligible participants will receive an introductory call informing them of their group allocation and guiding them on how to begin engagement with the study activities. All assessments will be conducted through an online survey, and feedback will be obtained over the phone from both groups at the end of the 4-week intervention period. A follow-up telephonic interview will be conducted 1 month after the postintervention assessment to ascertain help-seeking inclination and help-seeking behavior. The flow of the study is depicted in Figure 1.

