Help-seeking behavior from a mental health professional will be assessed at baseline, postintervention assessment, and follow-up through a single yes or no item. If help is sought, details on the nature of professional consultation, duration since first consultation, type of treatment, and satisfaction with consultation will be assessed [27]. If professional consultation for mental health concerns has not been sought since participation in the study, the reasons for not seeking consultation will be explored through an open-ended item.

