### Data Analysis Plan

Quantitative analyses will be conducted using SPSS Statistics (version 31.0; IBM Corp). Baseline characteristics will be summarized descriptively. Differential attrition will be examined by comparing dropout rates between groups using chi-square tests and by assessing baseline differences between completers and noncompleters using appropriate statistical tests. Sensitivity analyses will be conducted as needed based on the observed pattern of missing data.

Occurrence of professional help-seeking at the postintervention assessment and follow-up will be compared between groups using proportions, chi-square tests, and odds ratios with 95% CIs, with Cohen *h* reported as the effect size. As this behavioral outcome has no baseline variation in the nontreatment-seeking study sample, this will be treated as a completer analysis involving participants who provided postintervention assessment data.

For continuous outcomes, linear mixed-effects models will be used to estimate group, time, and group×time effects under an intention-to-treat framework. In addition, completer-only analyses will be conducted as exploratory comparisons to describe observed change among participants with complete data. A 2-sided significance level of .05 will be used.

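### At the end of the intervention the yes/no primary item is assigned to the online survey and the concurrent phone contact to feedback only, so primary answers that the call could obtain may be lost

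*Protocol article*

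**What the plan says.** - **Mode at the end of the intervention.** Procedure: "All assessments will be conducted through an online survey, and feedback will be obtained over the phone from both groups". Ethical Considerations adds that the baseline and postintervention surveys are run electronically in REDCap.
- **Primary outcome.** Data Collection Instruments: help-seeking from a mental health professional is measured at baseline, postintervention and follow-up "through a single yes or no item".
- **Content of the feedback.** Feedback Items lists distress severity, app use, difficulties, usability, perceived benefits, likelihood of recommending the intervention and an open question on impact. Whether a professional was consulted is not listed.
- **Follow-up.** Procedure plans a telephone interview 1 month later that does ask about help-seeking behavior.
- **Analysis set.** Data Analysis Plan, on the primary outcome: "this will be treated as a completer analysis involving participants who provided postintervention assessment data".
- **Expected loss.** Power Calculation: "A sample size of 150 participants per group has been estimated", "allowing for up to 33% attrition commonly observed in minimally guided digital interventions".

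**The concern.** Together these statements describe a participant who does not return the web survey, answers the planned call, rates the app's usability, and still has no primary value. Under the Data Analysis Plan's wording that person is outside the primary analysis set. A positive answer at the 1-month call might not bring them back, because completers are defined by postintervention data.

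The burden of the two routes differs. The online postintervention assessment holds long scales (K10, 10 items; GHSQ, 14 items; barriers scale, 28 items), while the primary outcome is one question that can be asked in seconds.

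More is at stake than precision. A completer comparison with a third of values missing can be biased if survey return is related to having sought help, or is related to it differently in the two arms. The plan takes this risk seriously enough to test for differential attrition. Obtaining the answer removes the problem for that participant, whereas an analysis can only make assumptions about it.

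**Working it through.** **Inputs.** From Power Calculation: 25% vs 10%, 150 per group, up to 33% attrition, "with 80% power at a 5% significance level using G*Power 3.1". From Data Analysis Plan: "A 2-sided significance level of .05 will be used". From Procedure: 1:1 allocation. Not in the documents: the share of survey non-responders who would answer the item by phone. I assume 0% to 75%.

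**Step 1: reproduce the plan's figure.** Pooled normal formula, with p̄ = (0.25 + 0.10)/2 = 0.175:

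n = [1.96·√(2·0.175·0.825) + 0.8416·√(0.25·0.75 + 0.10·0.90)]² / 0.15²
= [1.96·0.5374 + 0.8416·0.5268]² / 0.0225 = 99.5, so 100 per arm.

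Inflated for attrition: 100/0.67 = 149.3, so 150 per arm. The stated figure reproduces, and the 33% loss is already paid for.

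**Step 2: numbers analysed if the call recovers some answers.** At 33% loss about 50 of 150 per arm have no value. With recovery share r, n ≈ 100 + 50r.

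**Step 3: power and precision.** Normal formula: power = Φ[(0.15·√n − 1.96·0.5374)/0.5268]. At n = 125: (1.677 − 1.053)/0.5268 = 1.184, giving 88.2%. The 95% CI half-width for the difference is 1.96·√(0.2775/n). Exact enumeration of the uncorrected chi-square test is shown beside it.

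| Recovered (assumed) | n per arm | Missing | Power, normal | Power, exact | CI half-width |
|---|---|---|---|---|---|
| 0% | 100 | 33% | 80.2% | 81.6% | 10.3 points |
| 25% | 112 | 25% | 84.5% | 85.6% | 9.8 points |
| 50% | 125 | 17% | 88.2% | 88.7% | 9.2 points |
| 75% | 137 | 9% | 90.9% | 91.7% | 8.8 points |

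With no loss at all (150 per arm) the normal formula gives 93.2%, which is the ceiling. Gains should be read down one power column. Setting the normal 80% against the exact 89% would overstate the gain, which at 125 per arm is 8.0 points (normal) or about 7 points (exact).

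**Step 4: exposure to bias.** With no assumption about the missing answers, the possible range of an arm's help-seeking proportion is as wide as its missing fraction: 50/150 = 33 points with no recovery, and 25/150 = 17 points if half are recovered. This is the larger benefit.

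**The case against.** The case against is substantial, and parts of it stand.

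- **A reader might infer that the primary outcome is collected only online throughout the trial.** It is not. The sentence after the quoted one has it asked by telephone at the 1-month follow-up, so the point is confined to the postintervention time point. The same fact shows that the team already accepts telephone ascertainment of this outcome.
- **A reader might infer that primary data are certain to be lost.** The article does not say the call will not ask the item or chase an outstanding survey. The section on the item names no mode, and the flowchart and schedule figures are not shown. Call scripts are also detail that an article may leave to the full protocol. What remains is what the article does state: assessments online, feedback by phone, and a feedback list without the item. Hence "may be lost".
- **A reader might infer that the trial is underpowered or the sample size wrong.** Step 1 shows otherwise.
- **The recovery rate is unsupported.** People who leave a digital study may not answer the call either. This stands, so the range starts at 0%, where the gain vanishes.
- **The remedy has its own risks.** The trial is unblinded and the outcome is self-reported. If survey return differs by arm, verbal answers to trial staff would enter the arms unequally. Recruitment began in September 2025, so some participants may already have passed this time point under the current procedure. These risks stand, but they can be limited by a common script and made visible by recording the route.

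**Conclusion.** The point holds as a low-cost design improvement at the postintervention time point. It is not an error in any stated figure. As written, someone reachable by a planned call can lack a primary value and fall outside the primary analysis. The possible benefit runs from nothing (no recovery; about 80% power) to about 91% power at 75% recovery by the normal formula. At 50% recovery, power is 88%, the CI half-width is 9.2 instead of 10.3 points, and missing primary data fall from 33% to about 17%. These figures rest on the plan's 25% vs 10%, on attrition reaching the full 33%, on equal loss in both arms, and on an assumed recovery rate. The change is worth making; confidence is moderate because the call script is not in the article.

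**What to change.** 1. For anyone whose postintervention survey is outstanding, put the help-seeking item first in the end-of-intervention call, before any feedback question, with an identical script in both arms.
2. State in the Data Analysis Plan that an answer by either route counts as postintervention primary data.
3. Record the collection route, and report the primary result with and without phone-collected answers, with the number of phone answers per arm.
4. For those still missing, use the consultation timing reported at the 1-month call to fill postintervention status in a sensitivity analysis only, because that timing is recalled.
5. Document the date of the change, since the trial is under way. If the full protocol already has the call ask this item, say so in the Procedure section.

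**Cost:** one scripted question in a call already planned, one REDCap field, and a documented mid-trial change to how the primary outcome is collected. The price is mixed-mode, unblinded verbal reporting for part of the sample, possibly unequal between arms.

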**Figure 1 figure1:**
[figure not shown]
Flowchart of the study procedure.

### Interventions

#### Overview of MindNotes (Minimally Guided App-Based Intervention)

MindNotes has been described in an earlier section. It is a multimodule mobile app with sections designed to enhance self-awareness of mental health concerns, reduce help-seeking barriers, and build self-help skills. The intervention group will be requested to complete the self-discovery section of the MindNotes app and explore the breaking barriers section, as well as any other self-help sections as per their preference over 4 weeks. During this period, 2 reminders to encourage engagement with the app will be sent over WhatsApp (Meta Platforms). As part of the minimal guidance strategy, 4 brief personalized notes will be sent from the professional connect section of the app on a once-a-week basis to educate, clarify doubts, and motivate app use. The professional connect messages will be personalized based on the participant’s baseline distress, self-reported concerns, and their exploration of various sections of the MindNotes app. These messages will involve the communication of empathy, prompts to explore various sections of the app, and encouragement to apply what is learned through app exploration.

#### Overview of Mood Monitoring–Based Intervention

Mood monitoring apps can serve as credible active control conditions because they engage participants in regular self-reflection and emotional tracking without delivering targeted therapeutic content [28]. Moreover, mood tracking has been shown to improve emotional self-awareness and reduce depressive symptoms through increased insight and regulation, making it a psychologically active but nonspecific comparator in this study context involving help-seeking behavior as the primary outcome variable [29].

The participants in the control group will be asked to engage with a mobile-responsive, web-based mood monitoring or mood-logging app for the same 4-week duration as the intervention group. They will be instructed to log their mood at least twice a day for 4 weeks on this mood monitoring app. This would involve rating their mood on a 7-point Likert scale measuring levels of pleasantness and unpleasantness and indicating the nature of their predominant emotion from a list of emotion words provided (eg, happy, guilty, angry, sad, etc). Additionally, they will receive 4 generic reminders to encourage mood tracking and engage in self-care, along with 2 educational messages focused on enhancing mental health awareness via WhatsApp. These messages will include basic and brief information on managing common mental health concerns without any personalized elements. Overall, the mood-logging web app, along with a few educational messages, is expected to serve as an active control by controlling for nonspecific factors such as user engagement, expectancy effects, and digital interaction while offering a credible low-intensity self-help strategy to gain self-awareness.

To summarize, in addition to the opportunity to engage with the respective apps (MindNotes or mood-logging web application), both groups will receive 6 messages through the 4-week period of the study. The intervention group will receive 2 generic reminders alongside 4 personalized professional connect messages. The control group will receive 4 generic reminders and 2 educational cards focused on mood tracking, self-awareness, and emotional well-being. These reminders and messages are strategically distributed throughout the 4-week study period to promote participant engagement with either the MindNotes app or the mood-logging app within a minimal guidance framework, as shown in Table 1.

**Table 1 table1:** Details of the timing and contents of messages for both groups.

Day	Intervention group	Control group
6	Professional connect message 1: motivational message encouraging exploration of the “self-discovery” module and consistent app use	WhatsApp educational card 1: psychoeducation about mood tracking and encouragement to begin
10	WhatsApp reminder 1: inviting exploration of the “breaking barriers” section	WhatsApp reminder 1: promotes mood check-ins and reflection using the mood-tracking app
12	Professional connect message 2: reminder to continue exploring the app	WhatsApp reminder 2: encourages mood tracking and self-reflection at the 2-week mark
18	Professional connect message 3: based on the backend activity of each user, recommends sections to explore	WhatsApp educational card 2: offering general tips on managing moods
20	WhatsApp reminder 2: Promotes further engagement with self-help strategies	WhatsApp reminder 3: reiterating the importance of tracking mood and understanding emotional patterns
22	Professional connect message 4: final motivational message, encourages ongoing self-care and engaging in any remaining sections of the app	WhatsApp reminder 4: encourages end-of-trial reflection and sustaining self-monitoring practices

### Data Collection Instruments

The demographic and basic data sheet will be used to collect demographic information. In addition, the basic data sheet will include items assessing prior consultations with mental health professionals (if any), significant life events or ongoing stressors, and available sources of support during difficult times. To assess self-perceived common mental health concerns, participants will respond to an item regarding their current experience of depressive and/or anxiety symptoms. This item will inquire whether they are currently experiencing (1) persistent sadness or loss of interest in previously enjoyable activities; (2) frequent feelings of nervousness, tension, or anxiety; (3) both; or (4) none of the above. The duration of these concerns will also be captured using predefined categories ranging from less than 2 weeks to more than 6 months. Perceived severity of distress and its interference with daily functioning will be measured using a 5-point Likert-type scale, and another item will capture any current engagement in professional help-seeking. Participants will also respond to an open-ended item about the 3 self-help methods they use most frequently. Additional items rated on a 5-point Likert scale will assess the perceived usefulness of self-help strategies, self-rated perseverance in pursuing personal goals, and interest in learning self-help skills for mental health and well-being.

The K10 is a 10-item standardized measure of distress related to anxiety and depression symptoms over the past 4 weeks. It has demonstrated good psychometric properties in varied samples [25,30,31]. A total score of ≥20 indicates significant psychological distress and potential mental disorder [25]. The scores on this tool will be used to recruit eligible participants for the study (distressed nontreatment-seeking individuals). Participants who score 20 or above on K10 will be included in the study. The scores will also be used to document changes, if any, in psychological distress during the course of the study (secondary outcome).

Suicidal ideation—2 brief items developed for the study will be used to determine significant suicidality based on frequency and controllability. This is for screening out those who may need immediate support and referral. The first item asks, “In the past month, how often have you had thoughts about suicide?” with response options ranging from never (coded as 1), rarely or 1-2 times (coded as 2), sometimes (coded as 3), often (coded as 4), and all the time (coded as 5). The second item asks, “When feeling very sad or emotionally distressed, and thoughts of self-harm or suicide arise, how much control do you feel you have over acting on these thoughts?” Responses are rated as able to control easily (coded as 1), able to control with some difficulty (coded as 2), able to control with great difficulty (coded as 3), not able to control (coded as 4), and not applicable—do not experience such thoughts (coded as 5). All participants who report rarely having suicidal thoughts with great difficulty or no control; those who report sometimes having suicidal thoughts with great difficulty or no control, or those reporting often having suicidal thoughts, regardless of how much control they report, will be excluded.

Help-seeking inclinations will be assessed through the use of the General Help-Seeking Questionnaire (GHSQ). This 14-item scale will be used to assess the likelihood of seeking help from various sources (eg, parents, friends, helpline, and mental health professionals) for current mental health concerns or psychological distress, on a 7-point Likert scale [32]. Ratings on the item specific to mental health professionals will be the primary focus, although help-seeking inclination from various sources will also be documented. At follow-up, for the sake of minimizing respondent burden, help-seeking inclination only from mental health professionals will be assessed using the corresponding GHSQ items with a 7-point Likert-type scale.

The Barriers to Seek Professional Help for Mental Health Scale (BSPH-MHS) will be used to assess the severity and nature of perceived barriers to professional help-seeking for mental health concerns or psychological distress. It is a 28-item, 5-point Likert scale that evaluates perceived barriers across 4 domains: distress perception, stigma, service apprehensions, and instrumental obstacles with previous research supporting its reliability, construct, and convergent validity [30].

Help-seeking behavior from a mental health professional will be assessed at baseline, postintervention assessment, and follow-up through a single yes or no item. If help is sought, details on the nature of professional consultation, duration since first consultation, type of treatment, and satisfaction with consultation will be assessed [27]. If professional consultation for mental health concerns has not been sought since participation in the study, the reasons for not seeking consultation will be explored through an open-ended item.

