### Recruitment and Sampling

Participants will be recruited from the community through a multipronged strategy combining online and offline dissemination. This will include social media outreach, online announcements, and dissemination of posters in colleges, workplaces, and community locations. The inclusion criteria for the study are individuals aged 18 years and older, of all genders, fluent in English or Kannada, with at least 10 years of formal education, comfortable using a smartphone, experiencing self-reported current depressive or anxiety symptoms for 2 weeks or longer, and scoring 20 or above on the Kessler Psychological Distress Scale (K10) [25]. Participants will be excluded if they are currently receiving pharmacological treatment for any mental health condition, have attended 3 or more psychotherapy or counseling sessions in the past 3 months, or are presently engaged in counseling or psychotherapy. Individuals currently using any other mental health app, or those not amenable to participating in the study as assessed in a brief telephonic interview, or those having significant suicidal ideation as determined by responses on 2 items pertaining to the frequency and controllability of suicidal thoughts in the past 1 month, will be excluded from the study.

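### The written suicidality rule takes no action when a respondent reports no past-month suicidal thoughts but poor control over acting on thoughts of self-harm or suicide

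*Protocol article*

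**What the plan says.** The rule is set out in the protocol article, Methods, Data Collection Instruments, under suicidal ideation.

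- **Purpose of the items:** "This is for screening out those who may need immediate support and referral".
- **Item 1 (frequency):** "In the past month, how often have you had thoughts about suicide". The options are never (1), rarely or 1-2 times (2), sometimes (3), often (4) and all the time (5).
- **Item 2 (control):** it asks, when "thoughts of self-harm or suicide arise, how much control do you feel you have over acting on these thoughts". The options run from easy control (1) through some difficulty (2) and great difficulty (3) to no control (4). There is also a not-applicable option for people who "do not experience such thoughts (coded as 5").
- **Exclusion clauses:** there are three. The first is "All participants who report rarely having suicidal thoughts with great difficulty or no control". The second is "those who report sometimes having suicidal thoughts with great difficulty or no control". The third excludes anyone answering *often*, whatever the control answer.

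Recruitment and Sampling bases the exclusion on these answers and describes them as "2 items pertaining to the frequency and controllability of suicidal thoughts in the past 1 month". It separately excludes "those not amenable to participating in the study as assessed in a brief telephonic interview". Procedure says that this interview follows the questionnaires and includes a clinical look at the person's present mental state. Under Ethical Considerations, a supportive telephone session goes to people above the suicidality cutoff, and service suggestions are available to participants whenever needed.

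**The concern.** The rule treats one control answer in two ways. Someone who had suicidal thoughts once or twice in the month and could barely control acting on them is excluded and offered support. Someone who gives the same control answer but ticks *never* on frequency passes, and the text links no query to that answer.

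The pair is not necessarily a contradiction, because the two items differ in scope. Item 1 covers suicide only, in the past month. Item 2 adds self-harm and states no period. A person with self-harm urges but no suicidal thoughts, or with suicidal thoughts more than a month ago, could give both answers honestly. Choosing code 3 or 4 also means passing over the not-applicable option.

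What is at stake is participant safety. The trial enrols distressed people (K10 of 20 or above) who are not in current treatment, so a treating clinician cannot be assumed as back-up. For this pair, the written rule makes no use of the answer that most suggests a need for help, and the telephone session tied to the cutoff is not triggered.

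**Working it through.** No figure in the plan needs reproducing. The check applies the written clauses to every possible answer pair.

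**Inputs** (all from Data Collection Instruments): five options on item 1, five on item 2, three exclusion clauses.

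**Step 1. All pairs.** 5 × 5 = 25.

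**Step 2. Literal reading** (*often* means code 4 only).

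| Item 1 | Item 2 codes excluded | Pairs excluded |
|---|---|---|
| never | none | 0 |
| rarely | 3, 4 | 2 |
| sometimes | 3, 4 | 2 |
| often | 1 to 5 | 5 |
| all the time | none named | 0 |

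Excluded: 2 + 2 + 5 = 9. Passing: 25 − 9 = 16.

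**Step 3. Sensible reading** (*all the time* treated as *often*). Excluded: 9 + 5 = 14. Passing: 25 − 14 = 11.

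**Step 4. Poor-control pairs only** (item 2 = 3 or 4). There are 5 × 2 = 10.

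- Literal: 2 + 2 + 2 = 6 excluded and 4 pass (*never* and *all the time*, two each).
- Sensible: 2 + 2 + 2 + 2 = 8 excluded and 2 pass (*never* only).

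The two *never* pairs pass on both readings.

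**Step 5. After the fix, with *all the time* treated as *often*.** 14 pairs excluded, 2 clarified, and 9 passing as now (*never*, *rarely* and *sometimes*, each with item 2 = 1, 2 or 5: 3 × 3 = 9). Check: 14 + 2 + 9 = 25.

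**Step 6. Number of people.** Pair counts are not probabilities, and the documents give no frequency. Purely as an assumption, let a share p of the planned 2 × 150 = 300 participants give this pair. The expected number is 300p and the chance of at least one is 1 − (1 − p)^300.

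- p = 0.1%: 0.3 people, 25.9%.
- p = 2%: 6 people, 99.8%.

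This range has no basis in the documents and spans nearly every conclusion. It counts answers, not confirmed risk, and makes no allowance for people whom the eligibility call would stop. The conclusion does not rest on it.

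**The case against.** The best defence has four parts.

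**Recall period.** Recruitment and Sampling describes both items as covering the past month. On that view, *never* with poor control is mainly a mistake or a reply to a hypothetical, which the opening of item 2 invites. This stands in part, and it is why the pair calls for a question and not automatic exclusion. It does not close the gap, because respondents answer item 2 as worded, with self-harm included and no time limit.

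**Design choice.** The target is significant suicidal ideation, so requiring some recent ideation before control counts is coherent. That is fair as a definition. But the stated purpose is to find people who may need immediate support, and an admitted inability to control acting on self-harm or suicidal thoughts bears directly on that.

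**Existing safeguard.** The eligibility call is described without restriction to flagged people and may detect the risk. A full protocol, not shown, may tell interviewers which answers to probe. This lowers the chance of harm. The point rests on the rule as stated, with items, codes and clauses all given, and not on detail a condensed article would omit.

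**Consistency of reading.** A reader might infer that these two are the only poor-control pairs that pass. That holds only if *often* includes *all the time*, which the text does not say. Literally, two *all the time* pairs pass as well.

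**Conclusion.** The point holds for the written rule: *never* with item 2 code 3 or 4 prompts no action, while the same control answer with *rarely* or *sometimes* excludes. The extent is 2 of 25 answer pairs, or 2 of 10 poor-control pairs, on either reading of *often*. The number of people is unknown.

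A reader might go further and infer that people at high risk will be enrolled unnoticed. The documents do not support that. Many such answers may be inconsistent or hypothetical, the general clinical call may already catch some true cases, and help is available to participants throughout. Nor is there any consequence for the outcome analysis, sample size or power.

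The conclusion assumes that the clauses are applied as printed and that item 2 is put to everyone; no skip after *never* is stated. Priority is low to moderate. The change is still worth making because the gap concerns safety, enrolment is ongoing and the remedy uses a step already in place.

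**What to change.** Add one line to the rule in Data Collection Instruments: item 2 = 3 or 4 with item 1 = *never* is clarified in the existing eligibility call, before randomisation.

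- If poor control over current self-harm or suicidal thoughts is confirmed, exclude the person and offer the telephone session and referral described under Ethical Considerations.
- If it is not confirmed, for example because the answer was hypothetical or a slip, the person stays eligible.
- The same line can state that *all the time* is treated as *often*.

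The item wording need not change mid-trial.

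**Cost.** Notice to the ethics committee of a minor clarification, a few longer calls, possibly a few more exclusions, and a small difference in eligibility between earlier and later participants. No new items or visits are needed.

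A look-back at participants already enrolled is optional and a matter for the investigators' clinical judgement. Baseline answers may be months old, and a safety contact could itself prompt the professional help-seeking that is the primary outcome. If it is done, it should be the same in both arms and logged, and those contacted should be analysed in their randomised group.
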